#### Social Marginalization

Wilson et al [40] conceptualized transgender social marginalization as having three dimensions: homelessness, incarceration, and participating in commercial sex work. To more fully understand how these dimensions may be associated with routine HIV testing behaviors, participants will be asked about lifetime experiences of homelessness. Participants who have experienced homelessness will also answer whether or not they have been homeless in the past six months. Recent (<12 months) and lifetime history of incarceration, and recent (<3 months) participation in commercial sex work will be assessed by items from the *National Transgender Discrimination Survey* [41]. Commercial sex work is defined in this study as trading sexual activity or favors for food, money, a place to sleep, drugs, or other material goods.

#### Sexual Behaviors

Unprotected sexual intercourse remains the most common route of transmission for HIV in the United States [1]. However, according to the CDC, less than half of transgender men who received an HIV diagnosis in 2016 had any identified or reported sexual risk behaviors [1]. To collect more data on participants’ sexual risk behaviors, behavioral measures adapted from the National HIV Behavioral Surveillance behavioral inventory (and previously used with thousands of MSM by the research team [42,43]) will be used to collect information on sexual behaviors in the past three months. Participants will be asked to estimate the number of anal (and vaginal, if applicable) intercourse partners, as well as condom use or nonuse at each encounter, and the number of times they were the insertive (if applicable) versus receptive partner. The disclosure of HIV status and reported serostatus, or lack thereof, for each partner will also be assessed.

#### Intervention Acceptability and Satisfaction

This is the first study to pair telehealth with HIV self-testing in this population. Understanding how to improve the acceptability and satisfaction of this modality will benefit future studies. TY will report data on the acceptability of the experimental arm at the end of the follow-up period. Two different assessments will be used to measure acceptability: (1) the Self-Evaluation Form (SEF) [44] and (2) the Client Satisfaction Questionnaire (CSQ-8) [45]. The SEF is a brief 13-item questionnaire that elicits information regarding the participant’s experience with the intervention (ie, was the intervention interesting, was it relevant to their life). The CSQ-8 will be used to assess satisfaction with the intervention. The SEF and CSQ-8 will together take approximately 10 minutes to complete. Acceptability of the technology used in the intervention will also be assessed using a survey based on the Unified Theory of Acceptance and Use of Technology , which posits that an individual’s acceptance of a technology is a function of performance, effort, social influence, and facilitating conditions [46]. Technology usage will also be used as a proxy for acceptability, with server logs providing records of user sessions, session length, pages visited, and functions utilized.

#### Linkage to Care

It is important to introduce participants whose self-tests are positive to the HIV treatment cascade and continue following-up on their HIV testing frequency, sexual risk behaviors, and experiences with HIV stigma and transphobia. Per the recent recommendations of the Institute of Medicine [47], indicators of linkage to care will include: (1) attending at least one clinical care appointment, (2) having at least one CD4 test performed, and (3) having at least one viral load test performed within three months of HIV diagnosis [32,48].

### Statistical Analysis

The primary outcome will be the proportion of TY who tested for HIV at least once in the six-month follow-up period. Descriptive statistics of participant characteristics will be presented for all participants and also by study arm. These results will be compared using student t-tests or Wilcoxon rank sum tests for continuous variables, and Chi-square tests for categorical variables. The analysis for each outcome measure is described in detail below.

#### HIV Testing

Analyses will be conducted using logistic regression. The proportion of participants who obtain at least one HIV test within the follow-up period will be calculated for each study arm, along with corresponding 95% confidence intervals. First, the regression model will be fit using study arm only. A second model will control for baseline characteristics, as well as self-reported stigma and discrimination to measure their roles in mediating the outcome.

#### Sexual Risk-Taking

Sexual risk behavior will be defined as any unprotected anal or vaginal intercourse that occurs during the follow-up period with a person who is known by the participant to be HIV-positive, or has an unknown serostatus. The incidence of at-risk sex acts will be calculated as an incidence density, with the numerator being number of individual at-risk sex acts, and the denominator being person-years of follow-up time. Comparisons of the incidence of unprotected sex will be made by comparing incidence densities across arms. Incidence rates per person-year of follow-up will be estimated and compared using methods based on the Poisson distribution and using the generalized estimating equation (GEE) approach. Key covariates include demographic characteristics, previous HIV testing history, and reported stigmas and transphobia. Period incidence rates (three-month incidence density rates) of at-risk sex will be estimated by performing a GEE Poisson regression analysis of the trimonthly counts, implemented using SAS PROC GENMOD [49]. GEE models will control for demographic characteristics, baseline HIV testing history, and stigma, and will also be used to examine interactions between forms of stigma (HIV and transphobia) and sexual risk-taking.

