### Participants

Eligible participants will: (1) be aged 15-24 years; (2) have not tested for HIV in the last 12 months; (3) reside in the United States; (4) be willing to have HIV test kits delivered to an address they provide, (5) self-identify as noncis-gender; and (6) have access to a computer, smartphone, or tablet that can support the video-chat software VSee [27], which is an encrypted program compliant with the privacy requirements of the HIPAA.

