#### Demographics and HIV Knowledge and Testing History

The demographics section includes measures of age, education, race, ethnicity, sexual orientation, employment, and state of residence. Both the respondent’s sex assigned at birth and current gender identity will be collected. Previous literature on the sexual health of transgender individuals has been criticized for not using discrete categories for trans-masculine/transmale and trans-feminine/transfemale [33]. For this reason, current gender identity will include options for male, female, trans-masculine/male, trans-feminine/female, as well as categories for genderqueer/gender nonconforming, agender/genderfluid individuals, and a participant-driven response option. Items used in previous studies of LGBT persons will measure knowledge regarding the transmission and prevention of HIV [33,34], and knowledge and use of PrEP [34], at baseline and at each follow-up point.

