#### HIV Testing

History of HIV testing, including measures of frequency, place of testing, method of testing, and linkage to care (if HIV-positive), will also be collected at baseline. Follow-up surveys will repeat the questions from the baseline and will also ask questions regarding HIV testing since the last survey. These parameters include location of test (eg, home, Acquired Immunodeficiency Syndrome Service Organization, Department of Public Health, or physician), test result, care received (specifically for HIV-positive participants), and reason for testing (ie, routine care versus episodic exposure).

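### The GEE model for at-risk sex acts adjusts for demographics, testing history and stigma but not for the participant's own baseline three-month at-risk act count, which gives up precision

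*Protocol article*

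**What the plan says.** The Sexual Risk-Taking part of the Statistical Analysis section lists covariates twice. For the comparison of incidence rates: "Key covariates include demographic characteristics, previous HIV testing history, and reported stigmas and transphobia". For the regression models: "GEE models will control for demographic characteristics, baseline HIV testing history, and stigma". Neither list names baseline sexual behavior.

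The outcome is "any unprotected anal or vaginal intercourse that occurs during the follow-up period", with a partner who is HIV-positive or of unknown serostatus. It is modeled by a "GEE Poisson regression analysis of the trimonthly counts".

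Under Sexual Behaviors, items adapted from a national surveillance inventory "will be used to collect information on sexual behaviors in the past three months". They cover partners, condom use at each encounter and each partner's reported serostatus. The Measures section says that measures are collected at baseline, three months and six months. Under Study Procedure, randomization follows completion of the baseline survey and uses permuted blocks to balance arm size.

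On testing history, which is a listed covariate, eligible participants "have not tested for HIV in the last 12 months", and the baseline survey records "measures of frequency, place of testing, method of testing".

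**The concern.** The baseline value of an outcome is usually among its best predictors, and here it can be built at no cost. A model that leaves it out keeps between-person variation in the residual that could have been explained. If by chance one arm starts with more high-risk participants, the model has no term that accounts for it directly.

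Act counts are plausibly uneven across people (an assumption; the article gives no distribution). With about 100 completers per arm, baseline arm means could then differ noticeably by chance. At stake are the width of the confidence interval for the rate ratio and how readily a reader can trust it if baseline risk turns out uneven.

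**Working it through.** **1. Can the baseline count be built, and does it precede treatment?**

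| Needed | Where the article provides it |
|---|---|
| Same recall window as the outcome | Sexual Behaviors: past three months; outcome counts are also three-monthly |
| Unprotected anal or vaginal acts | Sexual Behaviors: partners, and condom use or nonuse at each encounter |
| Partner HIV-positive or of unknown status | Sexual Behaviors: serostatus, or lack of it, for each partner |
| Measured at baseline | Measures: baseline, three-month and six-month surveys |
| Measured before allocation | Study Procedure: randomized after the baseline survey |

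All five are met.

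**2. Does it enter the analysis some other way?** The outcome is confined to the follow-up period, so the baseline count is not one of the repeated measures. The blocks balance arm size, and no stratification by baseline risk is described. The count is in neither covariate list.

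**3. Number analyzed.** The article gives no precision or power figure for this outcome; the percentages in Sample Size are for the primary outcomes. Its retention arithmetic reproduces: 200 / (1 - 0.20) = 250 enrolled, so 200 completers, or 100 per arm at 1:1.

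**4. A rough linear guide.** In a linear model, adjusting for a baseline value with correlation r leaves a fraction 1 - r² of the variance: 0.91 at r = 0.3, 0.75 at 0.5 and 0.51 at 0.7. The planned model is a log-link Poisson model for counts, so this is only a guide, and the model type was simulated instead.

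**5. Simulation.** The model was Poisson log-linear with standard errors clustered on participant (GEE with independence working correlation), fitted to the three- and six-month counts with and without log(baseline count + 1), 600 replicates per scenario. From the article: 100 per arm and two follow-up counts. Assumed: a mean of 2 at-risk acts per three months; a true rate ratio of 0.7; a two-sided 5% level; and lognormal person-level rates with log SD 1.0, log SD 1.5, or log SD 1.0 with 40% structural zeros. The correlation is that of the underlying log rates between periods. The other listed covariates were not simulated.

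| Correlation | Variance of log rate ratio, adjusted / unadjusted | Reduction in variance |
|---|---|---|
| 0.3 | 0.91-1.02 | 9% to none |
| 0.5 | 0.79-0.85 | 15-21% |
| 0.7 | 0.61-0.77 | 23-39% |
| 0.9 | 0.36-0.49 | 51-64% |

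The confidence interval on the log scale shrinks by 1 minus the square root of the ratio:
- At 0.5: 1 - √0.85 = 8% to 1 - √0.79 = 11%.
- At 0.7: 1 - √0.77 = 12% to 1 - √0.61 = 22%.

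Power, unadjusted to adjusted, in the order log SD 1.0, log SD 1.5, structural zeros:
- At 0.5: 58% to 64%, 30% to 34%, 30% to 42%.
- At 0.7: 53% to 66%, 27% to 33%, 30% to 42%.

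These power figures are rough. With 600 replicates, a power near 30% has a simulation standard error of √(0.3 × 0.7 / 600) = 1.9 points. The nominal level may also be somewhat optimistic. At 0.7 with log SD 1.5, the unadjusted estimate has SD 0.33. Since ln 0.7 = -0.357, a normal calculation gives Φ(0.357/0.33 - 1.96) = 19%, against the simulated 27%. The variance ratios are the safer summary.

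**6. Bias and imbalance.** Both estimators centered on the true ratio of 0.7. At correlations of 0.7 and 0.9, the averages ran from 0.68 to 0.72 unadjusted and from 0.69 to 0.71 adjusted. The ratio of baseline arm means fell outside 0.80-1.25 by chance in 24-56% of simulated trials.

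**The case against.** This is one secondary outcome of a pilot, described in a condensed article. The first covariate list is worded as inclusive rather than complete, and a fuller list may sit in a document not shown. The unadjusted comparison is valid, and chance imbalance is already reflected in its standard error. The gain rests on a correlation nobody has reported and may be close to nil. A baseline covariate also does nothing about extreme counts that first arise during follow-up.

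Most of this stands and limits the weight of the point. It does not remove it, because the sentence on the GEE models names a specific adjustment set, and the baseline outcome is not in it.

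Four stronger readings are tempting, and the documents do not support them:

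- **That the rate ratio is biased.** Allocation is random, and both simulated estimators center on the truth.
- **That testing history is close to useless as a covariate because of eligibility.** Eligibility rules out only tests in the last 12 months. Never tested versus tested earlier, and how often, can still vary, and the article gives no distribution.
- **That adjustment is worth a fixed number of extra participants.** Any such figure from 1 - r² applies a linear-model formula with an assumed correlation to a log-link count model.
- **That the at-risk definition is wrong because it ignores PrEP.** The outcome is a coherent behavioral one, and the Discussion names STI as well as HIV transmission. PrEP is measured separately ("knowledge and use of PrEP [34], at baseline and at each follow-up point"), and nothing shows that its use is dated closely enough to classify individual acts.

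Nor do the documents rank sexual risk-taking above the other secondary outcomes.

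**Conclusion.** The point holds as a matter of efficiency. The stated model omits a pre-randomization covariate that the trial collects and that is likely to be prognostic. The cost is precision and unadjusted chance imbalance in baseline risk, not validity.

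The variance forgone is about 15-39% if the between-period correlation of log rates is 0.5-0.7, and almost nothing at 0.3. That range assumes the mean count, dispersion and rate ratio given above. It could be smaller if demographics, testing history and stigma already explain part of the same variation. The skewness of the counts is also an assumption. The change is worth making because it is nearly free, not because the present analysis would mislead.

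**What to change.** Pre-specify the baseline three-month at-risk act count as a covariate in the GEE Poisson model for the arm effect, in addition to the covariates already listed. Build it with the same definition as the outcome. Log(count + 1) is a suitable form, with an indicator for zero acts if many participants report none. Fix the form before outcomes are compared by arm, and include the term whether or not the arms look balanced at baseline, so that it cannot be seen as a choice made after the fact.

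The cost is one or two model terms and one sentence in the analysis section. No new data, visits or survey items are needed.

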#### Linkage to Care

The percentage of newly-identified HIV-positive participants who attend a comprehensive HIV care visit with a health care provider within three months of diagnosis will be tested for significance across the two study arms using logistic regression analysis. Demographic characteristics and self-reported stigma and discrimination will be controlled in these analyses.

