### Study Procedure

After providing consent electronically, participants will be directed to a short eligibility screener. If eligible, a potential participant will register for the study by providing their contact information. This information includes an email address, mobile phone number, physical mailing address, and preferred choice of name and pronouns. It is important to note that many TY have unstable housing or may not feel comfortable having mail, however discreet, sent to their home address. For this reason, the registration form will ask for a physical address to which the participant feels safe and comfortable receiving mail. As soon as the consent form, screening questionnaire, and site registration are complete, the participant will receive an email with instructions on completing the baseline survey. After completing the baseline survey, each participant will be randomized to either the control arm (HIV self-testing only) or intervention arm (video-based counseling in conjunction with HIV self-testing), using a 1:1 treatment allocation. The treatment assignments will be generated with the use of a pseudo-random number generator, which uses permutated blocks to ensure balance in the number of participants assigned to each arm. The randomization process will generate one of two emails to study participants, indicating whether they will be receiving HIV self-testing or video-based counseling plus HIV self-testing.

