### Sample Size

The research team proposes to enroll and maintain a sample of 200 TY aged 15-24 years. In order to achieve this target, recruitment efforts will continue until approximately 250 TY are enrolled. Allowing for 20% loss to follow-up, this approach will produce a sample of 200 TY who are expected to complete the prospective pilot RCT. As a comparison, an ongoing RCT of couples’ HIV counseling and testing in MSM [44] has a retention rate of 90-95%, making a 20% loss-to-follow-up a generous allowance. The sample size is calculated based on the detection of significant changes in each of the outcomes between the control and intervention groups. If data are pooled across participants’ gender identities, the study will have 81%, 92%, and 99% statistical power to observe differences of 10%, 12%, and 15% in the primary outcomes, respectively.

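### The adjusted logistic test of linkage to care is confined to newly HIV-positive participants, who are probably too few to fit it

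*Protocol article*

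**What the plan says.** The Linkage to Care paragraph of the Statistical Analysis section defines the endpoint as "The percentage of newly-identified HIV-positive participants who attend a comprehensive HIV care visit with a health care provider within three months of diagnosis". It says that this percentage "will be tested for significance across the two study arms using logistic regression analysis", and adds: "Demographic characteristics and self-reported stigma and discrimination will be controlled in these analyses".

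The HIV Testing paragraph of the same section treats the primary outcome differently: a model with study arm alone comes first, and an adjusted model second. For linkage, the adjusted model is the only one described.

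The Sample Size section states that "The sample size is calculated based on the detection of significant changes in each of the outcomes" between the two groups. The power figures that follow (81%, 92% and 99% for differences of 10%, 12% and 15%) concern only what that section calls the primary outcomes. The article nowhere states how many new HIV diagnoses are expected.

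**The concern.** The denominator is not the randomised sample but the few participants in it who are newly found to be HIV-positive. A logistic model with many covariates needs several events for each parameter. If there are fewer people than parameters, the covariates can predict every outcome perfectly: the estimated odds ratios run off to zero or infinity, and the Wald p-values mean nothing. Linkage to care is a secondary outcome and one of the aims given in the Introduction, so followed as written the plan would probably give an unusable result for a stated aim. The sample-size statement also leads a reader to believe that the trial was sized for this comparison.

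**Working it through.** **Inputs from the article.**
- Size (Sample Size section): "recruitment efforts will continue until approximately 250 TY are enrolled". A loss of 20% is then assumed, leaving 200 completers. Allocation is 1:1 (Study Procedure).
- Test sensitivity: 93.64% (Introduction).
- Prevalence: 22%. This is the only numerical HIV prevalence given. It refers to all transgender women living with HIV, so it includes infections already diagnosed.
- Covariates: the Measures section lists seven demographic items (age, education, race, ethnicity, sexual orientation, employment, state of residence) and three scales of enacted or internalised stigma.

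**Assumptions, not in the article.**
- New-positive yield of 1% to 10%.
- Linkage of 60% in one arm and 85% in the other.
- One degree of freedom per covariate, giving arm + 7 + 3 = 11 parameters besides the intercept. Coding race or state as categories would add more.

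**1. The article's own figure.** 200 / (1 − 0.20) = 250, which reproduces. That is about 100 per arm retained and 125 per arm enrolled.

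**2. Expected new positives.** Without allowance for sensitivity, 1% to 5% of 200 is 2 to 10 people. With it, expected detected positives = N × yield × 0.9364. The last two columns give the simulated chance that the table of arm by linkage has a zero cell, so that even the model with arm alone has no finite odds ratio.

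| Yield | Positives, N = 200 | Positives, N = 250 | Zero cell, N = 200 | Zero cell, N = 250 |
|---|---|---|---|---|
| 1% | 1.9 | 2.3 | 99% | 98% |
| 2% | 3.7 | 4.7 | 93% | 88% |
| 3% | 5.6 | 7.0 | 83% | 74% |
| 5% | 9.4 | 11.7 | 60% | 49% |
| 10% | 18.7 | 23.4 | 26% | 18% |
| 22% | 41.2 | 51.5 | 4% | 2% |

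**3. Can the adjusted model be fitted?** Data were simulated with arm and 10 covariates (four continuous, six binary), 300 runs per size, and each data set was checked for separation or rank deficiency by linear programming. Share of runs with no finite or unique maximum-likelihood solution:

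| Positives | 12 or fewer (4, 6, 9, 12 tried) | 20 | 28 | 41 | 52 |
|---|---|---|---|---|---|
| No usable fit | 100% | 95% | 58% | 16% | 3% |

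The first column is expected: with the intercept there are 12 coefficients, so 12 or fewer people can be fitted perfectly.

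**4. Events per parameter at 22%.** The smaller outcome class is non-linkage, on average (0.40 + 0.15) / 2 = 0.275 of positives.
- N = 200: 41.2 × 0.275 = 11.3 events; 11.3 / 11 = 1.0 per parameter.
- N = 250: 51.5 × 0.275 = 14.2 events; 14.2 / 11 = 1.3 per parameter.

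**5. Power for 60% against 85%, unadjusted.** About 13% to 15% at a 5% yield and 43% to 52% at 22%. Power of 80% would need 49 positives per arm.

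**6. Could an exact test reach p<0.05 at all?** With the most extreme table, Fisher's two-sided p is 0.10 for 3 against 3, 0.029 for 4 against 4, 0.029 for 3 against 4 and 0.048 for 2 against 5. Summing over all splits for which the smallest possible p is below 0.05, with positives in each arm binomial (n, yield) and no allowance for sensitivity:

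| Yield | 100 per arm | 125 per arm |
|---|---|---|
| 2% | 10% | 22% |
| 3% | 37% | 59% |
| 5% | 85% | 95% |

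These are chances that significance is attainable, not power.

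**The case against.** The yield is not in the article. The Introduction cites 22% for transgender women and says that prevalence is believed to be similar in other transgender groups. At that level the adjusted model would usually converge. This stands as a limit on confidence. But the figure counts everyone living with HIV, whereas the linkage analysis counts new diagnoses only, and even there the model has about one event per parameter.

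The parameter count is inferred. The survey items show what is collected, not what enters the model, and covariate selection, coding and penalised or exact fitting could be settled in an analysis plan that is not shown. This also stands in part: the absence of a fallback is no fault in a condensed article. What the article does fix is an adjusted significance test, and with so few people a shorter covariate list may not be enough: at yields of 2% and 3%, arm alone often has no finite odds ratio.

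Linkage is a secondary outcome of a pilot. That is true, and the primary comparison is unaffected.

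A reader might go further and infer that no test of linkage could ever be significant. The documents do not support that. The requirement of at least four positives in each arm applies only if the arms are equal; uneven splits can reach p<0.05, and at a 5% yield an attainable table is the usual case. Fisher's test is also not the planned test.

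A reader might also infer that the three-month window is broken for everyone. It is not. Surveys are timed from the study test, so positives on the study kit have a full window. Only diagnoses made after month 3 may lack one by the six-month survey.

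Finally, positives are shown to a counsellor in one arm and self-entered online in the other. That is a separate limit on comparability, which the change below does not remove.

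**Conclusion.** The concern holds as a probable, not a certain, failure. If the yield of new positives is between 1% and 5%, the adjusted model built from the listed measures cannot be estimated. If it were as high as 22%, the model would usually converge but would be heavily overfitted and, for a difference of 25 percentage points, have roughly even power or less. A significant unadjusted exact result is unlikely at yields of 2% to 3% but cannot be ruled out. The statement that the sample was sized for each outcome is unsupported for linkage: no power is given for it, and no number of positives from which power could be worked out. Confidence is moderate, because the yield, the linkage rates and the covariate count are all assumed.

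**What to change.** 1. In the Linkage to Care paragraph of the Statistical Analysis section, replace the covariate-adjusted logistic test with a descriptive report: number linked over number newly diagnosed in each arm, with exact 95% confidence intervals. An unadjusted exact comparison may be added if it is labelled exploratory.
2. Count separately those diagnosed too late to complete the three-month window by the final survey.
3. In the Sample Size section, limit the statement on what the sample was sized for to the primary outcome.
4. When reporting, mention that positives are ascertained differently in the two arms.

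The cost is a change of wording and the loss of the adjusted linkage comparison. Recruitment, data collection and the primary analysis stay as they are.
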